
D.2.2. Study Population:  There are about 9,000 first visit antenatal attendees per year in the ANC clinic at Umlazi Section D Clinic. Women range in age between 16 and 40 years. Approximately 25% are primagravid and the average gestational age at first visit is 28 weeks. Sixty percent of the women at the Umlazi ANC clinic have attended school for at least 8-10 years. Based on the most recent service statistics from the Umlazi Section D clinic, 21,369 women have been offered HIV testing since the program started in June, 2001. Of these women, 18,163 (85%) agreed to be tested, of whom, 8,173 (45%) were HIV infected. The transmission rate from mother to child is 34%, with approximately 95% transmission taking place during the pre and intrapartum period and the remainder post partum, primarily through breastfeeding. The prevalence in the clinic rose from 4% in 1990 to 46% in 2004.  

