D.4.7. Post Intervention Assessment: The follow-up assessment will be scheduled to coincide with women's 14 week and 9-month post-partum return visit to the clinic for the Expanded Program on Immunization (EPI).  At 14 weeks, a pap smear will be performed, STI testing will be repeated and a post-intervention behavioral survey will be conducted.  At 9 months post partum, the post-intervention behavioral survey will be repeated. The value of doing the post intervention behavioral assessment twice is that the first time period will capture the immediate intervention effect and the second time period will establish whether or not the behavior change was sustained over time. Both of the surveys will be conducted in a private room at the Umlazi Clinic.  The surveys will also be administered by an interviewer using CAPI (computer assisted personal interview). The survey interviewer will ask the questions and enter the participant's response directly onto a laptop computer. This mode of data capture improves data quality as the data will be entered on the computer one time only.  Each computer will be password protected and locked up at the medical school at the end of each working day.   

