D.8.Behavioural and clinical Assessments:  The survey instrument will be developed following standard practices.  The items will be written in Zulu, pre-tested on a few respondents, exit interviews will be conducted to determine if the content was understood as expressed, changes made, and then the survey will be translated into English by an independent translator to determine whether the content remains as planned.  Alterations will then be made, back-translated into Zulu and then pre-testing will be conducted a second time, with approximately 20 representative respondents.  Scales and variables that will be used to measure the key study outcomes such as emotional distress, social support, MTCT acceptance, and partner uptake of VCT will go through another version of refining and re-pilot testing with an additional 20 women. See Appendix 11 for a table of constructs, variables and measures to be used in the survey assessments.  The instrument development will take place during the phase of ethnographic research.  

D.8.1. Primary Outcomes
D.8.1.1. STI Incidence:  Incidence of STIs will be measured and compared among women in the intervention and control arms. Women are screened for a range of STIs upon enrollment to the ANC clinic including (Neisseria gonorrhea, Trichomonas vaginalis, Syphilis, and Chlamydia trachomatis) at baseline.  All women who test positive for any STI are treated immediately.   For the purpose of our study we will measure incidence of Neisseria gonorrhea, Trichomonas vaginalis, and Chlamydia.  These three organisms offer advantages in the evaluation of behavior change interventions in that they are curable with a single-dose treatment regimen and they are sufficiently prevalent in the target population to warrant inclusion.101  All women who return for the follow-up visit 14 weeks post-partum will be re-screened for Neisseria gonorrhea, Trichomonas vaginalis and Chlamydia. All women in the intervention and control arms who are screened for STIs at 14 weeks, will also have a PAP smear done at the time of the cervico-vaginal examination.  Women found to have an STI at this visit will be treated at that visit.   We feel it is important to include a biological outcome as one of our primary study outcomes to measure intervention efficacy. This will enable us to triangulate our findings from self-reported risk behavior data we gather from the women to gain a more complete understanding of behavior change.72  

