D.9.2. Aim 2:  We have conducted power analysis for each primary study outcome.  We have determined that reduction in STI incidence is the factor driving the sample size for the study.  Table 3 below shows the sample size required to detect significant differences in STI incidence across the two arms.  The criterion for significance (alpha) for all power analyses has been set at 0.05.  The tests are 2-tailed, which means that an effect in either direction can be detected and interpreted.   We hypothesize that the intervention will lead to lower rates of STIs. Prevalence data on STIs among pregnant women from KwaZulu-Natal indicate that 52% of women had at least one STI, 12.9% were diagnosed with Chlamydia, 7.8% were diagnosed with Neisseria gonorrhea, and 23% were diagnosed with Trichomonas vaginalis8.  Based on earlier research our team conducted in Durban we established the incident rate of gonorrhea among a periurban sample of ANC attendees in 2000 was 23%.  We have estimated a 22% annual incidence rate of either Neisseria gonorrhea, Trichomonas vaginalis or Chlamydia among HIV-positive women and 18% among HIV-negative women.    Results shown in Table 3 indicate that a sample size of 279 HIV-positive women and 295 HIV-negative women will be adequate to detect a minimum of a 9% difference in rate incident STIs among HIV-positive and an 8% difference among HIV-negative women in the intervention and control arms at the 9-month follow-up assessment.  We feel that this is the minimum level of change that would be meaningful from a policy and program perspective.

Table 3:  Required sample size per arm to detect a difference in STI incidence
STI incidence (base rate)	Effect size (% point change) and Required total sample size per arm	
	.08	.09	.10	
HIV+ women (.22) 	361	279	221	
HIV- women (.18) 	295	226	177	

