The primary purpose of the quantitative data analysis is to conduct a stratified analysis comparing HIV-positive and HIV-negative women randomized to the standard versus the enhanced counseling on the primary study outcomes described in Aim 2.  We have the following primary hypotheses to test intervention effect among women randomized to the intervention as compared to women randomized to the comparison arm at the 9-month post-intervention assessment: (H1) There will be a significant decrease in sexual risk of HIV as measured by STI incidence, correct and consistent condom use and partner testing.  (H2) There will be a significant decrease in mother to child transmission risk as measured by increased uptake of HIV VCT, increased uptake of ARVs, increased adherence to national infant feeding guidelines and increased contraceptive uptake. (3) There will be a significant improvement in psychosocial outcomes associated with PMTCT participation as measured by an increase in perceived social support, and a decrease in emotional distress and partner violence.  Statistics used to test these hypotheses will include comparisons of outcome variables across independent variables using contingency table analysis (log linear Poisson models) with Chi-square tests for significance, t-tests, and F-test for appropriate bivariate differences and multivariable analysis (ordinary least squares multiple regression for continuous outcome variables, and logistic regression for dichotomous outcome variables).  Diagnostic tests for multicollinearity will be conducted prior to multivariable analysis.  All analyses will be conducted separately for HIV-positive and HIV-negative women, given that the baseline rates vary between the two groups and expected change from pre to post-intervention assessment also varies by HIV serostatus.  We will examine how HIV serostatus disclosure to partners influences the effect of the intervention on each study outcome by including HIV serostatus disclosure as a covariate in our analyses. To compare operational outcomes across study arms (Aim 3) we will use contingency table analysis with Chi-square tests for significance and t-tests and F-tests for appropriate bivariate differences.   

D.12. Qualitative data analysis:  

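### STI incidence, which sets the sample size, is planned as an annual risk compared at 9 months, but the only repeat STI test is at 14 weeks post-partum; over that shorter period the planned proportional effect has roughly 50% power.

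*Protocol*

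**What the plan says.** D.9.2 states that "reduction in STI incidence is the factor driving the sample size for the study". It gives the control-arm assumption as an annual figure ("We have estimated a 22% annual incidence rate" in HIV-positive women, 18% in HIV-negative women) and uses .22 and .18 as the base rates in Table 3. From that table it takes 279 HIV-positive and 295 HIV-negative women per arm, for differences of 9 points and "an 8% difference among HIV-negative women in the intervention and control arms at the 9-month follow-up assessment".

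D.11 frames all the primary hypotheses as a comparison with "women randomized to the comparison arm at the 9-month post-intervention assessment". STI incidence is the first measure named under H1.

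The assessment schedule differs. D.8.1.1 says "All women who return for the follow-up visit 14 weeks post-partum will be re-screened for Neisseria gonorrhea, Trichomonas vaginalis and Chlamydia". D.4.7 lists STI testing at the 14-week visit. For the later visit it says only "At 9 months post partum, the post-intervention behavioral survey will be repeated". No section schedules an STI swab at 9 months.

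**The concern.** There are two linked problems. First, the protocol fixes two incompatible times for the same outcome. The sample size and H1 are set at 9 months, while the specimen is taken at 14 weeks. Read literally, H1 cannot be tested on STI incidence.

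Second, correcting the label alone is not enough, because the base rates in Table 3 are annual. D.2.2 says that "the average gestational age at first visit is 28 weeks", and the baseline STI screen precedes randomisation (D.4.4). An annual risk is therefore a fair approximation to what a woman accumulates by 9 months post-partum, but it is about twice what she accumulates by 14 weeks. STI incidence sets the size of the trial and is described in D.8.1.1 as its biological primary outcome. The protocol should therefore show what the planned numbers can detect at the test that will actually be done.

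**Working it through.** **Inputs from the protocol.** Control risks .22 and .18, annual (D.9.2); differences .09 and .08; 279 and 295 per arm; two-sided tests, with "The criterion for significance (alpha) for all power analyses has been set at 0.05"; normal approximation (D.9.3); first visit at 28 weeks' gestation on average (D.2.2); repeat swab at 14 weeks post-partum (D.4.7, D.8.1.1).

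**Assumptions not in the protocol.** Delivery at 40 weeks; constant hazard; 1:1 allocation; 80% power (the protocol says only that power is adequate).

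**1. Reproduce Table 3.** The pooled normal formula per arm, with p̄ = (p1+p2)/2, is

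n = [1.96·√(2p̄(1−p̄)) + 0.842·√(p1(1−p1)+p2(1−p2))]² / (p1−p2)²

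- HIV-positive, .22 against .14, .13, .12: 360.8, 278.6, 220.3, rounded up to 361, 279, 221.
- HIV-negative, .18 against .10, .09, .08: 294.1, 225.1, 176.4, rounded up to 295, 226, 177.

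All six cells match, so the table is arithmetically right for its inputs and its implied power is 80%.

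**2. Exposure.**
- To the 14-week swab: (40 − 28) + 14 = 26 weeks.
- To 9 months: 12 + 39 = 51 weeks.

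Over 51 weeks the control risks are .216 and .177 and power is 79% in both strata. The annual rates therefore suit a 9-month swab that is not scheduled.

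**3. Convert to 26 weeks**, using 1 − (1 − p)^(26/52).
- HIV-positive control: 1 − .78^0.5 = .117.
- HIV-negative control: 1 − .82^0.5 = .094.

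**4. Power for the planned effect at 279 and 295 per arm.** The planned relative reductions are .09/.22 = 41% and .08/.18 = 44%.

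| Scaling to 26 weeks | HIV-positive | Power | HIV-negative | Power |
|---|---|---|---|---|
| Constant hazard in both arms | .117 v .067 | 53% | .094 v .051 | 52% |
| Same relative reduction | .117 v .069 | 49% | .094 v .052 | 50% |
| Linear (p × 26/52) | .110 v .065 | 47% | .090 v .050 | 48% |

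The expected difference is 4.5 to 5.0 points in HIV-positive women and 4.0 to 4.3 points in HIV-negative women. Letting exposure run from 22 to 30 weeks across these scalings gives power of about 40-58%.

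**5. Detectable at 80% power over 26 weeks** (control risks .117 and .094).
- HIV-positive: 6.6 points, a 56% relative reduction.
- HIV-negative: 5.7 points, a 60% relative reduction.

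**6. The literal 9- and 8-point differences.** .117 v .027 and .094 v .014 have about 99% power, but they require relative reductions of .09/.117 = 77% and .08/.0945 = 85%.

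**The case against.** Several stronger readings are tempting, and the protocol does not support them.

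- *A reader might infer that the 9- and 8-point differences can no longer be detected.* They can, with about 99% power, because the variance is smaller at a lower base rate. What falls is power for the same proportional effect. The protocol states its targets in points, so the 41% and 44% are derived from its figures and are not declared by it.
- *A reader might infer that Table 3 is miscalculated.* It is not. The base rate and the observation period do not match.
- *A reader might infer that the swab comes too soon after the intervention*, since the third session is only four weeks earlier. But the video, the enhanced pre-test session and the first post-test session with condom skills fall around enrolment (D.5.2.1 to D.5.2.3), and the third session mainly adds family planning. Women are exposed to the intervention for most of the interval.
- *A reader might infer that a null STI result is bound to be misread.* That is speculation. STI incidence is one of four H1 measures, and D.4.3 intends biological and behavioural measures to be read together.

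The conditional nature of the power figures is a fair objection, and it stands. A single swab detects infection present that day, and baseline infections are treated, so risk may not accrue evenly. The base rate is also uncertain: D.9.2 cites 23% for gonorrhoea alone, with no period given. At an illustrative annual composite of 30% or 35%, power in HIV-positive women for the same relative effect over 26 weeks would be about 65% or 74%. Both are still short of 80%, and the protocol chose 22%.

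**Conclusion.** The point holds as a timing contradiction and a mismatch between the base rate and the observation period. H1 and D.9.2 refer to an STI comparison at 9 months for which no specimen is scheduled. On the protocol's own annual rates, the 14-week swab gives about half-power for the planned proportional effect: about 47-53% at 26 weeks. The smallest relative reduction detectable with 80% power is 56% or 60%, not 41% or 44%. These figures rest on delivery at 40 weeks, roughly constant hazard, the 22% and 18% rates, 1:1 allocation, and 80% as the intended power. The direction holds across the 22-30 week range and all three scalings; the exact percentages do not deserve more precision than that. The contradiction between the sections needs no assumption.

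**What to change.** 1. Reconcile the STI assessment time across D.4.7, D.8.1.1, D.9.2 and D.11. If the 14-week test is the one done, say so in D.9.2 and in H1, and reserve the 9-month time point for the survey outcomes.
2. Rebuild Table 3 on the control risk over the period actually observed (about .12 and .09 for 26 weeks on the present annual rates). State the assumed exposure, the conversion used and the target power.
3. Restate the detectable differences and power for 279 and 295 per arm, in points and in relative terms, with a range over exposure and base rate.
4. Optionally, prespecify a supplementary test pooled across serostatus and stratified by it. It has about 79% power if the planned relative reductions hold in both strata. It need not replace the separate analyses by serostatus, which D.11 declares as the main purpose of the analysis.

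The cost is revised wording, one recalculated table and a less favourable stated relative effect. No extra women are needed.

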The primary purpose of the quantitative data analysis is to conduct a stratified analysis comparing HIV-positive and HIV-negative women randomized to the standard versus the enhanced counseling on the primary study outcomes described in Aim 2.  We have the following primary hypotheses to test intervention effect among women randomized to the intervention as compared to women randomized to the comparison arm at the 9-month post-intervention assessment: (H1) There will be a significant decrease in sexual risk of HIV as measured by STI incidence, correct and consistent condom use and partner testing.  (H2) There will be a significant decrease in mother to child transmission risk as measured by increased uptake of HIV VCT, increased uptake of ARVs, increased adherence to national infant feeding guidelines and increased contraceptive uptake. (3) There will be a significant improvement in psychosocial outcomes associated with PMTCT participation as measured by an increase in perceived social support, and a decrease in emotional distress and partner violence.  Statistics used to test these hypotheses will include comparisons of outcome variables across independent variables using contingency table analysis (log linear Poisson models) with Chi-square tests for significance, t-tests, and F-test for appropriate bivariate differences and multivariable analysis (ordinary least squares multiple regression for continuous outcome variables, and logistic regression for dichotomous outcome variables).  Diagnostic tests for multicollinearity will be conducted prior to multivariable analysis.  All analyses will be conducted separately for HIV-positive and HIV-negative women, given that the baseline rates vary between the two groups and expected change from pre to post-intervention assessment also varies by HIV serostatus.  We will examine how HIV serostatus disclosure to partners influences the effect of the intervention on each study outcome by including HIV serostatus disclosure as a covariate in our analyses. To compare operational outcomes across study arms (Aim 3) we will use contingency table analysis with Chi-square tests for significance and t-tests and F-tests for appropriate bivariate differences.   

D.12. Qualitative data analysis:  

All in-depth interviews and FGDs will be audiotaped, transcribed, translated, coded and computerized for analysis.  Analysis of textual data will consist of two techniques: (i) the identification of recurrent patterns and themes:  Qualitative data analysis is the search for patterns in data and for ideas that help explain the presence of those patterns121.  Textual data will be carefully read to identify recurrent themes, and to obtain familiarity with complex interaction between men and women.  Codes will be created and assigned to specific sections of text so that the text can be easily and meaningfully searched122. After the coding scheme has been finalized, the ethnographers will be trained to apply the codes to the transcripts.  To ensure inter-coder reliability, 50% of data will be double-coded.  Coded text can be later extracted from each of the interviews so that a more domain-specific reading can be undertaken. We will import the translated, coded and computerized interviews and focus group discussion transcripts into Atlas ti, a qualitative analysis software package.  We will use Atlas ti to help identify recurring themes, concepts and terms that are relevant to the analysis.   (ii) Use of domain matrices:  Matrices and tables that categorize and display data will be used to help the reader quickly understand the dimensions by which the data are categorized and facilitate comparisons.  Matrices will help to display the full, yet condensed data set122. For example, a matrix may be developed to describe the decision-making process that women go through to discuss testing with their partners.  
 
D. Data management AND QUALITY CONTROL

D.13.1 Data management: Data will be primarily managed on-site by a data entry and management team.  
D.13.1.1  Survey data:  
Data will be collected through Computer Assisted Personal Interviews (CAPI).  We will pilot our questionnaires for the baseline survey in 2 different ways. Firstly, we will conduct cognitive interviews with 5 women to evaluate our baseline survey. During these interviews, we will ask each woman the questions within each section of the baseline survey. At the end of each section, we will ask each woman a series of questions about the content of the section in order to assess their understanding of each question, to determine whether the response categories are sufficient, and to evaluate whether questions need to be added, deleted or altered. Following the cognitive interviews, we will make any necessary changes to the baseline survey instrument. We will then pilot the baseline survey in its entirety with 15 women from the Umlazi Section D clinic. 

D.13.1.2 Qualitative Data: 
Ethnographers will conduct the in-depth interviews in Zulu.   Field guides for the semi-structured in-depth interviews and focus group discussions will be translated into Zulu and back translated into English prior to use. All interviews will be audiotaped.  Ethnographers will be responsible for transcribing each interview.  We will employ a translator who will translate the Zulu transcripts into English.  The data entry team will then computerize these English transcripts for analysis purposes.  The data manager will supervise staff, and there will be regular quality assurance checks conducted to assure consistency in methods of translation and transcription. The qualitative data files will be backed up on a daily basis on all project hard drives, the South African Co-PIs' hard drive and on CD-ROM.  Qualitative interviews will be randomly checked for content, accurate transcription and translation.  

D.13.2.  MONITORING QUALITY CONTROL: 
D.13.2.1. Protocol compliance
a.	The Project Coordinator will be responsible for auditing 100% of the informed consents to ensure that consent for participation in the study was obtained according to Good Clinical Practice (GCP). 
b.	Counseling Observations: The staff psychologist will be responsible for observing 5% of the patient's visits at baseline, 6 weeks and 10 weeks. These sessions will be randomly sampled. The staff psychologist will have a checklist to verify that the content of the session adheres to the protocol. The psychologist will also evaluate the quality of the nurse's counseling. These evaluations will be used to maintain quality of care in delivery of services across both the control and intervention arms. 
c.	Exit Interviews: The survey interviewers will be responsible for conducting exit interviews with 5% of the participants following the baseline, 6 week and 10 week sessions. These sessions will be randomly sampled. These interviews will address perceived quality of services received and they will be used to maintain quality of care or improve quality of care as needed across both the control and intervention arms. 

D13.2.2 Quality Control IN DATA MANAGEMENT
a.	The Project Coordinator will be responsible for auditing 5% of the patient's medical charts at the baseline, 6 week and 10 week visit for protocol compliance. These charts will be randomly selected.  The audit will involve a comparison between the woman's antenatal card and the infant's road to health card with our Medical Extraction Form. The nurses will extract a number of pieces of valuable information from these cards onto our Medical Extraction Form . We want to ensure that the nurses are reliably extracting information from these two sources into our Medical Extraction Form.
b.	The Project Coordinator will also be responsible for validating 5% of data captured by the data capturer.  She will verify data captured on the database against the Medical Extraction Forms.

D.14. Data Safety and Monitoring Plan: 
 Our data safety and monitoring plan includes the establishment of a Data Safety and Monitoring Board (DSMB).  The DSMB will be responsible for general oversight of the study including reviewing study protocols, monitoring project implementation including accrual and drop out rates, reviewing interim analyses of outcome data, and monitoring adverse events and human subjects issues.  The DSMB will establish clear stopping rules for the trial if adverse events are deemed to reach an unacceptable level, if drop out rates across study arms are unacceptably different, if interim analysis indicates that the intervention effect is significant enough to warrant that all women in the trial be given access to the intervention, or if it becomes apparent that the trial cannot be concluded successfully. Interim analyses will be planned each year during the intervention implementation phase.  The primary risk to participants in this trial is the potential social harms that may be associated with HIV diagnosis.  We will ask study participants to return to the research site as well as provide participants with a card containing information on how to contact the research staff to report such incidents as HIV-related family disruption, acts of discrimination and physical harm.   Research staff in both arms of the study will be trained to complete descriptions of adverse events that will then be sent electronically to the U.S. PI and the South African Co-PI's.  All adverse events and serious adverse events associated with the procedures will be appropriately reported to the JHU Committee on Human Research, the University of KwaZulu-Natal IRB and the DSMB.  We define adverse events as any undesirable, unintended reaction or event (whether expected or unexpected) that results from study procedures or study interventions.  We define serious adverse events as any subset of adverse events that are fatal, life threatening, require hospitalization, or prolong existing hospitalization or result in persistent or significant disability.  No serious adverse events are expected with study activities. Adverse events and serious adverse events will be reported to IRBs within the required time frame that each IRB specifies.  The time frame for reporting to the IRB at the University of KwaZulu-Natal is within 7 days, and to the JHU IRB we are required to report the event within 10 days of being detected. We propose reporting adverse events to the DSMB within 10 days of an adverse event coming to the attention of a PI and within 5 days for serious adverse events.
 

D.15. Project Management:  

The project will be managed jointly by the PI, [name], and the Co-PI [name].  [name] will be responsible for overall quality of the study, adherence to the study protocol, data management, analysis of study data, scientific integrity of the study results, interpretation of the study results and dissemination of the study findings.  [name] will also oversee the overall financial management of the project and will coordinate the transfer, cleaning and quality control of the study data.  [name] will be responsible for management of the South Africa-based staff, oversee the scientific aspects of the study in South Africa and the financial management of the South Africa-based activities.  Quarterly site visits by either [name] or the U.S. Study Coordinator will be arranged.  Regular bi-monthly conference calls will be scheduled with [name] to assure that monitoring of activities is maintained.  We will hire two Study Coordinators for the project, one based in North Carolina and one based in South Africa.  The responsibilities of these two study coordinators will be to backstop the PI and the Co-PI's to ensure the overall quality of the study.  

D16.  Staff Training:
 
All project staff will undergo extensive training on the goals and study procedures, as well as in-depth training on specific duties and responsibilities.  We will develop a manual of operations that will be regularly updated and reviewed with the staff.  We will conduct an annual staff retreat in which we will refresh staff on the study procedures.  The different categories of staff will undergo specific training related to their responsibilities.  The counselors will be trained by [name] (co-investigator) a trained clinical psychologist specializing in HIV related counseling.  The counselors will build counseling skills through role-plays with clients. Prior to study implementation each counselor must conduct a 'certification' counseling session.  Based on satisfactory scores counselors will be 'certified' to begin study implementation.  Every year counselors will receive a refresher course and will be required to get re-certified.  

D17.  Limitations: 

As in most prospective studies, this study is limited by selection bias.  However, the study's timeframe is not long enough to raise significant concerns over uncontrolled temporal effects.  The Umlazi SED ANC clinic has considerable experience in following up individuals for extended periods of time and has demonstrated in previous studies that loss to follow-up can be kept to about 10% per year.  It is also possible that women who are most likely to experience difficulty disclosing results to their sexual partner and who may be most likely to suffer from negative outcomes as a result of disclosure, will choose not to participate in the study.   Since we will randomize women to either the intervention or comparison arm, this bias should be evenly distributed between arms, and therefore we will be able to still determine the relative effect of the intervention in this population of women. 

E.  Human Subjects 

Research ethics experience of the study team:  The research team has considerable experience with research ethics.  The PI, [name], works extensively with the Johns Hopkins University Bioethics Institute, as the Assistant Director of a fellowship program in International Research Ethics for scientists from sub-Saharan Africa.  She has been involved with facilitating short-course ethics training in Malawi, Ethiopia, and Tanzania.  She is also involved in an empirical study designed to describe research participant understanding in HIV prevention studies in South Africa, Malawi, and Haiti.  All members of the study team have participated in NIH-funded studies in the past and have successfully completed human subjects training (certifications are attached). 

Voluntary choice regarding disclosure: We recognize the potential risks associated with HIV serostatus disclosure to sexual partners among women.  We have conducted prior research studies on the associations between HIV and violence against women and we have reviewed the literature extensively to further understand the positive and negative outcomes of disclosure for women.  There is some evidence to suggest that women who disclose HIV test results to their partners are at risk for experiencing negative reactions, including physical violence.  While the rates of HIV serostatus disclosure related violence are relatively low in the U.S. (between 0.5-4%) the risks of violence following disclosure among women in sub-Saharan Africa is higher (3.5%-14.6%).  The potential risks associated with disclosure have to be weighed against the possible individual and public health benefits of disclosure.  Expanded awareness of risk that comes with disclosure may enable couples to make informed choices about behavior change and reproduction that may ultimately lower the incidence of HIV.  There are also risks associated with not disclosing HIV test results with a sexual partner, including the risk of transmission to a partner and anxiety associated with concealing this information from a partner.  We have developed a counseling approach that is designed to help women more carefully weigh the risks and benefits of disclosure.   Through the intervention that we are testing in this proposal women will spend more time with the counselors discussing disclosure.  The HIV counseling will be client-centered, which means that the role of the counselor is to enable the client to make independent decisions related to disclosure.  Counselors will use a structured discussion counseling tool to help women assess their risk for physical harm if they disclose HIV positive test results to their partner.  We developed this tool based on the factors that were associated with disclosure-related violence in our earlier research among women in the HIV VCT clinic in Dar es Salaam.  The details of this screening tool have been described in section D.5.2.4.  

Value to Host Country:  This protocol responds to needs identified in the host country.  The study builds on capacity and has the potential to be of lasting value to host countries.  A report commissioned by the South African Department of Health provides an assessment of the national pilot PMTCT program1.  Among some of the recommendations made in the report it was stressed that there is a need to “provide on-going psychological and emotional support to HIV positive women as well as advice on disclosure.”  The proposed intervention directly addresses the social and behavioral challenges of implementing PMTCT interventions that have been identified in the South African Department of Health report.  

Voluntary informed consent:  The research site at Umlazi D Clinic in Durban, South Africa has extensive prior experience obtaining informed consent from women for clinical trials within this cultural context.  The informed consent procedures for this study have been designed to maximize understanding of potential risks.  All consent forms will be translated into Zulu and back-translated into English to ensure correct use of language.  Consent forms will be read aloud to participants by study interviewers.  After reading the consent forms prior to seeing a signature, interviewers will ask participants to summarize the study and explain the reasons why they want to participate.  At this point any misunderstandings regarding procedures, risk or benefits can be clarified.  If there are cultural, literacy or political reasons why a signature is not appropriate, individuals will be allowed to mark the consent form with an 'X'.  Separate informed consent will be obtained for each time that data are collected including the preliminary studies, the baseline survey, in-depth interviews with selected survey participants, exit interviews from specific counseling sessions, observation of specific counseling sessions and the 9-month post-partum follow-up survey.  Women will be informed during the consent process that their clinic charts will be reviewed by the study staff, and some data will be extracted, including information on their HIV testing decision, whether or not they received ARV prophylaxis for PMTCT, and the length of their counseling sessions.  

Confidentiality:  Successful implementation of the trial will require that strict confidentiality of all study participants be maintained.  Rapid HIV testing will be anonymous to afford the highest level of confidentiality.  For the survey and qualitative data collected as part of the study, participants will be assigned a unique identification number.  All data and information collected will be kept in locked filing cabinets.  Counselors, interviewers, data entry clerks, data manager and tracers will all be trained on procedures to maintain confidentiality and will be required to sign an oath of confidentiality prior to study implementation.  We will ask participants to return to the research site as well as provide them with a card that has contact information for research staff to report such incidents as HIV-related disruption of family, as well as physical and social harms.  This will enable research staff to make appropriate referrals to community-based agencies for ongoing support.  

Treatment for HIV:  Currently at the UMLAZI Section D ANC all HIV-positive pregnant women are offered the HIVNET 012 single dose Nevirapine protocol for prevention of mother-to-child transmission.  The protocol  includes treatment of opportunistic infections and prophylaxis.  The clinical care and drugs are at no cost to the mothers and infants and includes partners where available.  All HIV positive women and their infants are provided ongoing care at the Clinic.  Antiretroviral therapy (HAART) is available to HIV infected women with CD4 < 200 or Clinical Stage IV and their infants if also HIV infected. Women and children who are eligible for HAART are screened and receive adherence counseling at the SED Clinic. HAART is initiated at PMMH and women receive continuum of care at the clinic. Currently, about 5% of the patients at the Clinic are on potent anti-retroviral therapy that is accessed through their private health insurance or through participation in industry-sponsored trials currently underway at the Clinic and about 50 women have been prescribed ARVs through PMMH following delivery. 

Description of risks and strategies to minimize risk: 
